## Administration of Surveys

All subjects will complete a baseline and post-intervention survey. The baseline survey will collect basic demographics and baseline medication adherence and blood pressure monitoring frequency and be conducted over the phone after the participant has been consented. The post-intervention survey will collect similar adherence and monitoring information, as well as qualitative data regarding patient perceptions about the interventions. The post-intervention survey will be completed at the in-person 4 month visit. These surveys should take no more than 15 minutes to complete. Demographic and socio-economic questions are modified from demographic questions on the Behavioral Risk Factor Surveillance System survey, administered by the Centers for Disease Control and Prevention. **Provider interviews following the intervention period will collect clinician and care team perceptions about the interventions as well as feedback for improvement of future iterations. Provider interviews should take no more than 20-25 minutes to complete.**

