### 1.2 Consent Process

We are requesting a waiver of the requirement to document consent and HIPAA authorization with a signature for participants enrolled into this study since we believe the research presents no more than minimal risk of harm to subjects and involves no procedures for which written consent is normally required outside of the research context. A majority of participants being enrolled in this study will be enrolled via a remote recruitment process, therefore we will read the IRB approved Consent/HIPAA script over the phone to each patient and ask them to provide verbal consent and verbal HIPAA authorization for use of their data in the study. Once a patient provides verbal consent, the research coordinator will select this option on the Consent/HIPAA screen on the participant dashboard that was just created for participation on the WTH health web platform for this study. At this point, the participant is randomized into 1 of the 3 study groups. After randomization, the coordinator will inform the participant of their assignment and read the instructions for their study group. A copy of the consent form will also be mailed to the participant's home address. A copy of the Consent/HIPAA document will also be included in the recruitment mailings sent to all patients before being called by the study team. While we do ask that

participants come for an in-person end of study visit, it is likely that due to attrition many will not complete the final visit. As is such, we believe it impracticable to collect the signed consent form at this time, as we will end up with an incomplete record of written consent. Therefore, a waiver of the requirement to document consent and HIPAA authorization with a signature is requested.

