| 06/06/2018 | 
 
1. Update baseline survey
 
2. Add new partner "welcome" message
 
3. Add new partner "thank you"/end of study message
 
4. Update provider notifications
 
5. Update number of recruitment calls
 
6. Update recruitment letter
 
7. Add study staff
 
 | 
 
1. To reduce confusion and increase consistence, the baseline medication adherence question was modified to match the positive framing of the weekly text message.
 
2. Added to confirm partner enrollment into Way to Health, confirm partner's ability to receive text messages, and to thank them for their participation.
 
3. Added to signal the end of their participation and to thank them for supporting their participant.
 
4. As a research project adjunct to clinical care, providers are notified when their patient is enrolled in the study. Additionally, since BP is being monitored remotely for hypertension management, PCPs are notified of out of control BP measurements so medications can be adjusted for better control.
 
5. Initial data extraction yielded a smaller than expected number of potentially eligible patients. We are increasing the number of recruitment call attempts from 3 to 5 to ensure sufficient sample size for the study.
 
6. As stated in the enrollment procedures, the participant will receive a mailed copy of the consent document upon enrollment. Removed erroneous language in the recruitment letter that referred to review of the "enclosed consent documents" since they are not being mailed until the participant has verbally consented and enrolled.
 
7. Add [name], Research Coordinator.
 
 | 6/19/18    |

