# Final Statistical Analysis Plan

**\*\*New changes from initial protocol notated in bold, parts removed from initial protocol notated in strikethrough**

## Analysis Plan

### 1.1 Power and sample size

Assuming 5.3mmHg standard deviation of SBP (given variability of BP over time) and a two-sided significance level of 0.017 (to accommodate the three pairwise comparisons), our sample size of 60 in each intervention arm and 30 in the control arm provides 80% power to detect a difference in SBP reduction of 3.75 mmHg between either intervention and usual care, and a difference in SBP reduction of 3.1 mmHg between the remote monitoring and social influence arms. A preliminary data extraction shows about 2300 patients uncontrolled hypertensive patients in PFC, which should provide a sufficient population for enrollment. **However, based on additional clinical information obtained after the study was initiated, we estimate a standard deviation for change in SBP of 20mmHg, larger than our initial estimate. Thus, we increased our accrual target to 100 in each intervention arm and 50 in the control arm, which provides 80% power to detect a difference in SBP reduction of 11mmHg between either intervention and usual care, and a difference in SBP reduction of 9mmHg between the remote monitoring and social influence arms.**

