### 1.2 Data analysis

As ~~is standard in~~ a randomized controlled trial, ~~we will conduct~~ **our primary analysis will follow the intention to treat approach, in which participants are analyzed according to their assigned treatment regardless of compliance.** For patients with missing **blood pressure** data, we will first include ~~blood pressure~~ readings available from the **electronic health record (EHR)** occurring from 90-150 days from the participant's start in the intervention, and then conduct multiple imputation **using all available baseline covariates.**

The primary ~~outcome analysis~~ will relate the systolic blood pressure ~~during~~ at the 4 month visit to **assigned** intervention arm, adjusting for the initial systolic blood pressure by including ~~the~~ baseline measures in the model. ~~For patients with missing data who do not complete the 4 month in person blood pressure reading, we will conduct multiple imputation of the SBP values at 4 months as a function of baseline variables, including intervention arm.~~

Secondary analyses include ~~modeling~~ **analyzing achievement** of normotensive status ~~by study arm~~ using logistic regression **and repeating the analyses for systolic blood pressure with diastolic blood pressure at the 4-month visit. We will estimate** ~~ion of~~ recruitment and attrition rates, and ~~evaluation of~~ patient perceptions about the interventions from follow-up surveys. We will also compare medication adherence **and blood pressure monitoring adherence** by intervention arm after enrollment. We will adjust these analyses for BMI, age, gender, race, forgetfulness (from the baseline and follow-up survey), and diabetic status. In addition, we will track BP measurements **by arm** from the (EHR) that are obtained through usual care **for up to 8 months after the study intervention. We will as well as during** ~~also evaluate~~ PCP visits, MPM messaging, phone calls, hospitalizations, and medication changes. ~~for up to 8 months after the~~

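### The medication-adherence and normotensive models leave out baseline values that the trial already holds, which costs efficiency but not validity

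*Supplement*

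**What the plan says.** The final SAP, 1.2 Data analysis, relates 4-month SBP to assigned arm with baseline SBP in the model, and repeats that analysis for DBP. Normotensive status is analyzed by logistic regression. Medication adherence and monitoring adherence are then compared by arm, followed by: "We will adjust these analyses for BMI, age, gender, race, forgetfulness" and, to end the list, diabetic status. The final protocol carries the same list in Statistical Considerations 1.2, in Analysis Plan 1.2 and in Objectives 1.6. The last of these attaches it to medication adherence.

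On what is collected, Administration of Surveys says: "The baseline survey will collect basic demographics and baseline medication adherence and blood pressure monitoring frequency". The modifications log (06/06/2018) records that "the baseline medication adherence question was modified to match the positive framing of the weekly text message", so the baseline item and the on-study item were deliberately brought into line.

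On timing, the same survey section says that the baseline survey will "be conducted over the phone after the participant has been consented". Study Design 1.2 Consent Process says, once verbal consent has been recorded: "At this point, the participant is randomized into 1 of the 3 study groups". The participant is then told the arm.

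**The concern.** The baseline value of an outcome is often among its best predictors. The plan uses it for SBP and DBP. For medication adherence it includes forgetfulness, which is at best a partial stand-in, but not baseline adherence. For normotensive status it names no baseline BP, although how far above the threshold a patient starts should bear on whether the threshold is reached.

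At stake is the efficiency of secondary comparisons, some with only 50 controls, all of them to be repeated by enrollment round in smaller groups. Randomization is blocked, with no stated stratification on BP or adherence, so a chance imbalance on these variables would be handled only by the model.

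**Working it through.** **Step 1. The plan's own power figure.** Inputs from SAP 1.1: "two-sided significance level of 0.017 (to accommodate the three pairwise comparisons"; "we estimate a standard deviation for change in SBP of 20mmHg"; "we increased our accrual target to 100 in each intervention arm and 50 in the control arm". With power = Φ(δ / (σ√(1/n₁ + 1/n₂)) − z), z = 2.387 for two-sided 0.017:

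- 11 mmHg, 100 vs 50: 11 / (20√0.03) = 3.175; power 78.5%.
- 9 mmHg, 100 vs 100: 9 / (20√0.02) = 3.182; power 78.7%.
- Detectable at exactly 80%: (2.387 + 0.842) × 20√0.03 = 11.18 mmHg, and × 20√0.02 = 9.13 mmHg. These round to the stated 11 and 9.

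The plan's figures reproduce. They concern SBP; the plan claims no power for any secondary outcome.

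**Step 2. Linear model for adherence.** Adding a baseline covariate with correlation ρ to the outcome multiplies the residual variance by 1 − ρ². Leaving it out makes the variance 1/(1 − ρ²) times as large. The documents give no ρ, so it is an assumption shown as a range. Using 0.017 for a secondary comparison is also an assumption.

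| Assumed ρ | SE factor √(1 − ρ²) | Variance if omitted, 1/(1 − ρ²) | 80% power becomes | Detectable difference, 100 vs 50 (0.559 SD without baseline) | Detectable difference, 100 vs 100 (0.457 SD without baseline) |
|---|---|---|---|---|---|
| 0.2 | 0.98 | 1.04 | 82% | 0.548 SD | 0.447 SD |
| 0.4 | 0.92 | 1.19 | 87% | 0.512 SD | 0.418 SD |
| 0.6 | 0.80 | 1.56 | 95% | 0.447 SD | 0.365 SD |

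These are upper figures. The relevant ρ is what remains after the listed covariates, and baseline forgetfulness may already carry part of it.

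**Step 3. Logistic model for normotensive status.** The formula in step 2 does not apply here. A simulation used 100 vs 50, an 11 mmHg shift on SD 20 (the plan's SD of change, borrowed as the scale of follow-up SBP), a cut-point 0.25 SD below the control mean, two-sided 0.017 and 3,000 replicates per setting:

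| Assumed ρ | Power without → with continuous baseline BP | SE of log odds ratio | Median log odds ratio |
|---|---|---|---|
| 0.2 | 54% → 54% | 0.355 → 0.363 | 0.87 → 0.91 |
| 0.4 | 54% → 58% | 0.355 → 0.382 | 0.86 → 0.99 |
| 0.6 | 56% → 68% | 0.356 → 0.419 | 0.90 → 1.18 |

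The standard error rises, but the conditional estimate moves further from zero, so power is flat at 0.2 and rises at 0.4 and 0.6. With no effect, the rejection rate lay between 1.2% and 2.0% in every setting (2,000 replicates). Baseline BP must enter as a continuous term: entry requires an elevated reading at the last visit, so baseline normotensive status hardly varies.

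**Step 4. Timing of the survey.** The consent sections put randomization at the recording of verbal consent, with disclosure next. The survey section fixes only that the survey follows consent. In Procedures, the Enrollment paragraph comes before the Randomization paragraph and mentions demographics and medication details, but neither places the survey. The order is open.

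**The case against.** The strongest reply is that this is a preference for efficiency. The trial is called a pilot, the outcomes are secondary, and under 2:2:1 randomization the comparisons are valid without these terms. Chance imbalance is already allowed for in the standard error. That stands, and it rules out several stronger readings:

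- A reader might infer that the estimates are biased. They are not. In a particular sample, a 2-SE baseline imbalance would move an estimate that ignores baseline by 2ρ√0.03 SD, that is 0.07, 0.14 or 0.21 SD at ρ = 0.2, 0.4 or 0.6 (100 vs 50). This is chance error, not systematic error.
- A reader might infer that every secondary model omits its baseline. The DBP model includes it.
- A reader might carry the 50 controls over to monitoring adherence. The text prompts go only to the two intervention arms, and Objectives 1.6 compares monitoring adherence between those arms: 100 vs 100.
- A reader might treat baseline monitoring frequency as the same measure as monitoring adherence. The baseline item is self-report before any cuff or prompt, while the outcome appears to be response to prompts. It is a related covariate only.
- A reader might infer that the covariate list governs the normotensive model. The wording is unclear, and the protocol ties the list to medication adherence. Baseline BP is unnamed on either reading.
- A reader might infer that surveys were answered after the arm was known. The text leaves this possible; it does not show it.

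What the reply does not remove is that useful baseline values are on file and unused, while the plan uses them for SBP and DBP. The same covariate sentence also includes forgetfulness from the follow-up survey, a post-randomization variable. That is a separate matter, and this change does not resolve it.

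**Conclusion.** The point holds as a loss of efficiency in two named places: the medication-adherence model lacks baseline medication adherence, and the normotensive model names no baseline BP. For a linear adherence model, the variance is up to 4% to 56% larger than it need be over assumed correlations of 0.2 to 0.6, and less once the listed covariates are counted. For the logistic model, the simulated power gain runs from none at 0.2 to 12 points at 0.6 (56% to 68%), under the assumed shift, SD and cut-point. No correlation is in the documents, so the true size is unknown. The primary analysis is untouched. Survey timing is an open question, not a shown fault, but it comes first: an answer given after the participant knows the arm can be influenced by it and is then unsafe as a baseline covariate.

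**What to change.** In SAP 1.2, and in the matching protocol sections (Objectives 1.6, Statistical Considerations 1.2, Analysis Plan 1.2):

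- Add baseline self-reported medication adherence to the medication-adherence model.
- Name continuous baseline SBP and DBP in the normotensive logistic model, and say whether the existing covariate list applies to that model.
- Optionally add baseline monitoring frequency to the monitoring-adherence model (two intervention arms), described as a related covariate.

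In Administration of Surveys and both consent sections, state that the baseline survey is completed before randomization and disclosure of the arm. For participants already enrolled, verify the order from records before using their survey answers as baseline covariates.

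The cost is SAP and protocol wording, the order of the enrollment call, and a records check where enrollment has already happened. No new data are needed.

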Secondary analyses include ~~modeling~~ **analyzing achievement** of normotensive ~~status~~ **by study arm** using logistic regression **and repeating the analyses for systolic blood pressure with diastolic blood pressure at the 4-month visit. We will** estimate ~~ion~~ of recruitment and attrition rates, and evaluate ~~ion~~ of patient perceptions about the interventions from follow-up surveys. We will also compare medication adherence **and blood pressure monitoring adherence** by intervention arm after enrollment. We will adjust these analyses for BMI, age, gender, race, forgetfulness (from the baseline and follow-up survey), and diabetic status. In addition, we will track BP measurements **by arm** from the (EHMR) that are obtained through usual care **for up to 8 months after the study intervention. We will** ~~as well as during~~ **also evaluate** PCP visits, MPM messaging, phone calls, hospitalizations, and medication changes. ~~for up to 8 months after the study intervention using similar models. Lastly we will analyze diastolic blood pressure at the 4-month visit, adjusting for the initial diastolic blood pressure.~~ **We will repeat all analyses by sub-group related to time of enrollment (round 1 and round 2). Finally, we will perform a thematic evaluation of provider perceptions about the interventions from information gathered during follow-up telephone interviews as well as process data collected from a review of provider actions following monitoring encounters.**

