~~study intervention using similar models. Lastly we will analyze diastolic blood pressure at the 4-month visit, adjusting for the initial diastolic blood pressure.~~ **We will repeat all analyses by subgroup related to time of enrollment (round 1 and round 2). Finally, we will perform a thematic evaluation of provider perceptions about the interventions from information gathered during follow-up telephone interviews as well as process data collected from a review of provider actions following monitoring encounters.**

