### **Overall Perceptions of SupportBP**

We will ask about your perceptions of both the first round of the program as a provider with patients enrolled in the study and the second round with the encounters routed to the nursing pool.

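### The plan repeats every analysis within rounds 1 and 2 but gives no direct comparison of the arm effect between the rounds

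*Supplement*

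**What the plan says.** The Final Statistical Analysis Plan, section 1.2, closes its account of the secondary analyses with "We will repeat all analyses by subgroup related to time of enrollment (round 1 and round 2". The Final Protocol carries the same sentence in Statistical Considerations 1.2: "We will repeat all analyses by sub-group related to time of enrollment (round 1 and round 2".

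The primary model in the same section has two ingredients, assigned arm and baseline systolic pressure. The covariates named for the secondary analyses are BMI, age, gender, race, forgetfulness and diabetic status. Neither document gives a round term, an arm-by-round term, the round sizes, the event or date that separates the rounds, or a rule for reading a difference between them.

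The rounds do differ in how care was delivered. The modification log entry of 06/06/2018 has primary care physicians notified of out-of-control readings. The entry of 11/30/18 changes the notification procedure at the clinic providers' request. The Final Protocol (Procedures, Monitoring) sends these encounters to a nursing pool that reviews them with a nurse practitioner. Appendix A describes "the second round with the encounters routed to the nursing pool", and asks staff about the effect on blood pressure control in each round and about the change in workflow.

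**The concern.** Round is not an arbitrary subgroup. It marks a change in the clinical response to monitoring, so readers will ask whether the intervention worked better under one arrangement. Running each analysis inside each round gives two estimates and two p-values, but no estimate of the difference between them and no measure of its uncertainty.

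With each round holding only part of the sample, significance in one round and not in the other is a likely outcome even when the effect has not changed. Such a pattern could be credited to the change in alert handling.

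**Working it through.** **Inputs from the Final Statistical Analysis Plan, 1.1**
- Alpha: "two-sided significance level of 0.017 (to accommodate the three pairwise comparisons"
- SD: "we estimate a standard deviation for change in SBP of 20mmHg, larger than our initial estimate"
- Size: "we increased our accrual target to 100 in each intervention arm and 50 in the control arm"
- Target for each intervention arm against control: "80% power to detect a difference in SBP reduction of 11mmHg between either intervention and usual care"
- Target for the contrast of the two intervention arms, at the same power: 9 mmHg

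**Input assumed.** Round sizes are not stated. The log entry of 10/04/18 raises the target from 150 to 250, so I take 150 then 100 (60/60/30 and 40/40/20) and vary the split. No dropout is included, as in the plan's own calculation.

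**Step 1. Reproduce the plan's power.** Normal approximation: SE = SD × √(1/n₁ + 1/n₂), power ≈ Φ(Δ/SE − 2.387), where 2.387 is the two-sided 0.017 critical value.
- Intervention against usual care: SE = 20 × √(1/100 + 1/50) = 3.46. Power at 11 mmHg is 78.5%; the 80%-power difference is 11.18 mmHg.
- Between intervention arms: SE = 20 × √(2/100) = 2.83. Power at 9 mmHg is 78.7%; the 80%-power difference is 9.13 mmHg.

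Both detectable differences round to the stated figures, so the power statement stands.

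**Step 2. Power within each round, 11 mmHg against usual care.**
- Round 1: SE = 20 × √(1/60 + 1/30) = 4.47; power = 52.9%.
- Round 2: SE = 20 × √(1/40 + 1/20) = 5.48; power = 35.3%.

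**Step 3. Chance that exactly one round is significant when the true effect is the same in both.** The rounds are independent, so P = p₁(1 − p₂) + p₂(1 − p₁) = 0.529 × 0.647 + 0.353 × 0.471 = 0.342 + 0.166 = 0.51 (50.9% unrounded). Both rounds are significant 18.7% of the time and neither 30.5%.

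| Split | 11 mmHg vs usual care, alpha 0.017 | Same, alpha 0.05 |
|---|---|---|
| 50:50 | 49.4% | 47.5% |
| 60:40 | 50.9% | 49.3% |
| 70:30 | 55.1% | 54.5% |
| 80:20 | 61.7% | 62.8% |

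For the 9 mmHg contrast between intervention arms the 60:40 figure at alpha 0.017 is also 50.9%.

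**Step 4. Dependence on the true effect** (60:40, against usual care, alpha 0.017).

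| True effect in both rounds, mmHg | 0 | 5 | 7 | 9 | 11 | 13 | 15 | 20 |
|---|---|---|---|---|---|---|---|---|
| Exactly one round significant | 3.3% | 15.9% | 28.5% | 42.1% | 50.9% | 50.2% | 40.8% | 11.8% |

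**Step 5. The direct contrast.** A test of arm-by-round would declare a false difference at its own alpha (1.7% or 5%), whatever the common effect. Its SE at 60:40 is √(4.47² + 5.48²) = √(20 + 30) = 7.07 mmHg. The difference between rounds detectable with 80% power is 2.80 × 7.07 = 19.8 mmHg at alpha 0.05 and 3.23 × 7.07 = 22.8 mmHg at alpha 0.017. Power for an 11 mmHg difference between rounds is about 34% and 20% respectively.

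**The case against.** The strongest reply is that the plan never says it will infer a round difference from a pair of p-values. It says only that analyses are repeated, in the secondary paragraph of a trial whose abstract calls it a pilot. Purely descriptive round-specific results would fit that sentence. This stands: what is missing is a method for comparing rounds, and a misreading is a risk that the plan leaves open, not one that it commits.

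Second, about half the time is not a fixed property of the plan. The 11 mmHg is a detectable difference, not an expected effect, and the round sizes are undocumented. The log approves the larger sample on 10/11/18 and the notification change on 12/20/18, so a first round of exactly 150 is not established. This also stands, and the figure must carry its conditions.

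Third, the interaction would be weak, so a null result would say little. That is true, but it argues for an estimate with an interval. The width would show how little the data can say about the rounds, which two p-values hide.

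Two stronger readings are tempting and are not supported. A reader might infer that leaving round out of the primary model biases the pooled comparison. Allocation is 2:2:1 in blocks of 5 and 10 throughout (Final Protocol, Study Design 1.1), so arm is nearly unrelated to round and no bias follows. A reader might also infer that different kinds of patients entered each round. The logged eligibility changes were approved on 3/30/18 and 5/22/18, before both the sample-size increase and the notification change, and nothing else in the documents shows such a difference.

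**Conclusion.** The point holds in a limited form: the plan splits every analysis by round and provides no direct comparison of the arm effect between rounds, although the rounds differ in a way that invites one. If the common true effect is at the plan's own design difference, significance is compared at 0.017, and the split lies between 50:50 and 70:30, separate tests disagree in about 49% to 55% of trials. For small or large common effects they disagree much less often.

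These figures rest on the plan's SD of 20 mmHg for change, on the assumed split, and on complete data. The Final Protocol expects many participants to miss the final visit, which would lower the power within rounds. Adjustment for baseline pressure could raise it, but the documents give no correlation from which to say by how much. The pooled primary result and the plan's stated power are not in question.

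**What to change.** Add to section 1.2 of the Final Statistical Analysis Plan, and align the Final Protocol:
- Define the rounds by a date or event, and give their sizes.
- Fit one model with arm, round, baseline systolic pressure and arm-by-round. Report the interaction contrast for each pair of arms with its 95% confidence interval as the comparison of rounds.
- Give round-specific estimates with intervals as description, without separate significance claims.
- Say in advance that the contrast is imprecise: under the assumed split, an SE of about 7.1 mmHg against usual care and a detectable difference of about 20 mmHg (alpha 0.05) or 23 mmHg (alpha 0.017).

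A round main effect in the pooled primary model is optional. It may gain some precision and corrects no bias.

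The cost is a few lines of text, a round term and its interaction with arm; no new data are needed. The drawback is a wide interval that will usually be inconclusive about the change in alert handling.
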